## Abstract

**Background:**

Advanced lower extremity peripheral artery disease (PAD), whether presenting as acute limb ischemia (ALI) or chronic critical limb ischemia (CLI), is associated with high rates of cardiovascular ischemic events, amputation, and death. Past research has focused on strategies of revascularization, but few data are available that prospectively evaluate the impact of key process of care factors (spanning pre-admission, acute hospitalization, and post-discharge) that might contribute to improving short and long-term health outcomes.

**Methods/Design:**

The FRIENDS registry is designed to prospectively evaluate a range of patient and health system care delivery factors that might serve as future targets for efforts to improve limb and systemic outcomes for patients with ALI or CLI. This hypothesis-driven registry was designed to evaluate the contributions of: (i) pre-hospital limb ischemia symptom duration, (ii) use of leg revascularization strategies, and (iii) use of risk-reduction pharmacotherapies, as pre-specified factors that may affect amputation-free survival. Sequential patients would be included at an index “vascular specialist-defined” ALI or CLI episode, and patients excluded only for non-vascular etiologies of limb threat. Data including baseline demographics, functional status, co-morbidities, pre-hospital time segments, and use of medical therapies; hospital-based use of revascularization strategies, time segments, and pharmacotherapies; and rates of systemic ischemic events (e.g., myocardial infarction, stroke, hospitalization, and death) and limb ischemic events (e.g., hospitalization for revascularization or amputation) will be recorded during a minimum of one year follow-up.

**Discussion:**

The FRIENDS registry is designed to evaluate the potential impact of key factors that may contribute to adverse outcomes for patients with ALI or CLI. Definition of new “health system-based” therapeutic targets could then become the focus of future interventional clinical trials for individuals with advanced PAD.

## Background

Advanced lower extremity peripheral artery disease (PAD) represents a relatively uncommon, but exceptionally high-risk, manifestation of systemic atherosclerosis. Both traditional PAD classification systems and recent evidence-based PAD care guidelines have emphasized the potential benefit of more consistent case classification of advanced PAD into two distinct clinical syndromes, denoted as acute limb ischemia (ALI) or chronic critical limb ischemia (CLI). Both PAD syndromes represent manifestations of a severe compromise of arterial blood flow to the affected lower extremity, with the acuity of onset of ischemia and specific clinical signs used to distinguish between these syndromes [1]. In contrast to comparable acute coronary disease syndromes (such as the acute coronary syndromes [ACS] of non-ST segment myocardial infarction (MI) and ST-elevation MI), the epidemiology of ALI and CLI is much less well defined in the absence of population-based surveillance. Current evidence suggests an incidence of approximately 430 to 1160 cases per million individuals annually [2-4]. Although ALI and CLI represent the primary etiology of most lower-limb amputations [5] and are associated with high short-term rates of systemic and limb ischemic events [6,7], uncertainty regarding the incidence, prevalence, and outcomes of the ALI and CLI syndromes is, in part, based on the lack of a uniform and applicable definition used in either field studies or in clinical practice outside of specialized vascular centers.

Improvements in coronary ischemic syndrome health outcomes have been facilitated by consistent use of ACS definitions and subsequent evaluation of health system factors that contribute to cardiovascular risk. For example, improved outcomes for patients with ST-elevation MI and acute stroke were achieved by evaluation of methods to shorten end-organ ischemia time (including patient recognition of heart attack symptoms and creation of expedited referral systems) and this knowledge has been successfully encompassed in cardiac and stroke care guidelines [8,9]. In contrast, little data exist to define the contribution of limb ischemia time to adverse limb or systemic outcomes for individuals with ALI and CLI. Similarly, whereas the impact of pharmacological and behavioral risk-reduction interventions (e.g., use of antiplatelet and statin medications) is well-defined for patients with ACS, a knowledge gap exists regarding the potential impact of these systemic treatments after successful leg arterial revascularization. This knowledge gap is central for patients with advanced PAD as recent data document that both endovascular and open surgical approaches, while effective in improving limb outcomes for individuals with CLI [10], are still associated with very high rates of heart attack, stroke, and cardiovascular death within one year of an index CLI presentation.

Randomized clinical trials (RCTs) provide the most robust methodological approach to determining the efficacy, harm, and net impact of potential treatments for individuals with advanced PAD. Nevertheless, recent experience has demonstrated the challenges and costs associated with recruitment of individuals with ALI and CLI into prospective RCTs. As for coronary disease or heart failure clinical research, there are potential advantages to the study of outcome determinants from a prospective disease registry. These advantages include: enrollment of the full patient cohort with minimal exclusion criteria, the use of a multicenter design that is often more broadly representative of the ALI and CLI population than might be recruited from specialized centers that participate in sponsored RCTs, the potential to capture longer-term outcomes data, the ability to *pre hoc* define outcome determinants (e.g., pre-hospital leg ischemia time) that are not easily evaluated in a RCT context, and often the ability to collect such data at lower cost [11-13].

In this context, specific knowledge gaps regarding determinants of adverse health outcomes for individuals with ALI and CLI were used to design a hypothesis-driven clinical registry. The primary aim of the FRIENDS registry is to evaluate a pre-defined set of patient and health system factors on one-year rates of systemic and limb ischemic events, and thus on amputation-free survival. These factors included: (i) pre-hospital limb ischemia symptom duration, (ii) use of leg revascularization strategies, and (iii) use of risk-reduction pharmacotherapies. Outcome events (rates of non-fatal MI, stroke, amputation, and death) will be collected at one month, six months, and one year. Secondary study aims are to assess: (a) the relative frequency and etiology of the ALI and CLI diagnoses in a large community-derived population, (b) the frequency of use of evidence-based risk-reduction medication in this high-risk population at baseline and during follow-up, (c) predictors of functional status, and (d) rates of systemic ischemic events. The FRIENDS registry structure was *pre hoc* designed to serve as a pilot study for future implementation of a multicenter registry to prospectively evaluate the impact of standards of care on health outcomes for all individuals with ALI and CLI.

## Methods/Design

### Study design

The registry is designed as a prospective cohort evaluation of individuals with advanced PAD, defined as inclusive of the ALI and CLI syndromes.

### Enrollment

We defined the index hospitalization as the first presentation for ALI or CLI, since a hospital admission serves as an easily identified site for detection of such cases. Use of an index hospitalization is also advantageous (as compared to recruitment from vascular specialty clinics or wound centers) since it defines a population in whom health care resource utilization is high and in which quality outcomes staff now exist to facilitate initial and subsequent outcomes data collection. Patient enrollment is intended to be sequential and fully inclusive, with exclusions limited to non-provision of informed consent that are documented by a screening log.

### Definition of advanced PAD syndromes

The registry was designed to utilize definitions of advanced PAD (ALI and CLI) that are encompassed in the intersocietal “ACC/AHA Guidelines for the Management of Patients with PAD” [1] and concordant TASC-II [2] PAD guidelines. As such, ALI is clinically defined by the admitting vascular specialist in patients who experience the clinical stigmata associated with acute ischemia and a potential threat to limb viability of less than or equal to 14 days in duration. Using this guideline-derived ALI case classification, enrollment of patients is achieved via documentation of acute limb ischemic symptoms and signs (the 6 “Ps”) (Table 1). CLI will be defined, per these PAD clinical care guidelines, in patients with Rutherford class 4, 5, or 6 manifestations such as ischemic rest pain, and minor or major tissue loss of greater than two weeks duration. At enrollment, patients with ALI and CLI will undergo evaluation of an objective pedal or toe pressure measurement when this is feasible pre-revascularization. Source documents have been created so that collection of these entry criteria, as applied by participating clinicians, will be uniformly obtained.

**Table 1 T1:** Inclusion criteria: Ischemic symptoms and signs, and objective limb pressure measurements at enrollment

**For all patients: Clinical symptoms and signs**	**For ALI patients: Presence of any of the “6 Ps”**	**For all patients: Objective pressure measurements**
Ischemic rest pain	Pain	Pedal pressures
Ulcer	Pale	Great toe pressures
Gangrene	Pulseless	Ankle-brachial index
	Paresthesia	Toe-brachial index
	Paralysis	
	Poikilothermia	

*Abbreviations*: *ABI* Ankle-brachial index, *TBI* toe-brachial index.

### Use of source documents and data abstraction

This is a prospective registry, and as such all sequential eligible patients with ALI or CLI who are hospitalized (defined as requiring an index leg revascularization procedure or overnight stay) will be entered into the registry. Medical record documentation will be required immediately on admission (not retrospectively) for establishment of the presence of ALI or CLI. Vascular specialty and hospitalist staff will receive instruction on: (a) the clinical definitions of ALI and CLI, (b) how to complete a source document on patient admission that includes the time of onset of symptoms, and (c) the use of health system tools (e.g., standardized order sets) to facilitate prompt measurement of pedal or great toe pressures (Table 1).

A documented medical history of coronary artery disease (CAD) will consist of 1 or more of any of the following chart documented conditions or procedures: stable angina, previous myocardial infarction, history of percutaneous coronary intervention or history of coronary artery bypass graft surgery. Documented cerebrovascular disease (CVD) will be defined by a history of transient ischemic attack (TIA), ischemic or hemorrhagic stroke, carotid stenting or carotid endarterectomy. Documented prior PAD will be defined by 1 or more of the following criteria: symptomatic PAD defined by history of claudication, asymptomatic PAD documented in the medical records, or history of ALI or CLI.

Baseline height and weight will be obtained from the medical records, and body mass index (BMI) calculated. Patients will be considered overweight if they have a BMI of 25 kg/m^2^ to less than 30 kg/m^2^ or obese if they have a BMI ≥30 kg/m^2^. Atherosclerosis risk factors will be defined as present: if documented in the medical record, if the patient is receiving treatment for the risk factor at the time of study enrollment, or if there are supporting laboratory test data proximal to the index hospitalization. Diabetes will be considered present when there is chart documentation, regardless of type (I or II), or when use of an anti-diabetic medication or dietary intervention is documented. As well, the documentation of fasting blood glucose ≥7 mmol/l (126 mg/dl) will be considered evidence of diabetes when these laboratory data are available. Hypertension will be defined when chart documented or when there is evidence of treatment with any antihypertensive medication or behavioral intervention (e.g., use of calcium channel blockers, ACE-inhibitors, beta blockers, diuretics or diet/exercise). Dyslipidemia is considered present when there is chart documentation or use of any lipid-lowering or cholesterol modifying medication (e.g., statin, niacin, fibrates, or bile acid binding resin agents). Dyslipidemia is also considered to be present if, per the National Cholesterol Education Program (NCEP) guidelines, the total cholesterol concentration is >200 mg/dl (5.18 mmol/l), LDL concentration is >130 mg/dl (3.37 mmol/l), and/or HDL concentration is <40 mg/dl (1.04 mmol/l). Other criteria for establishment of dyslipidemia include a fasting triglyceride concentration of ≥200 mg/dl, or total cholesterol/HDL ratio ≥5.0. Smoking status is recorded as “current” if any cigarettes were used within one month of the encounter, “former” if smoking had ceased more than one month prior to the encounter, and “never” if there is no history of tobacco use. A family history of premature CAD consists of any chart documentation of a family history of premature CAD or any myocardial infarction (MI) in a first-degree relative (men <55 years or women <65 years). The etiology of ALI or CLI is coded from data obtained in the medical record.

Ambulatory status on admission and discharge will be obtained from patient self-report and supplemented by abstracted medical record reports of treating clinicians. There is at present no single well-accepted format for recording ambulatory status in individuals with ALI and CLI. Ambulatory status therefore will be categorized into five groups and assigned ordinal values of 1 to 5, with 5 representing the best, and 1 the lowest, ambulatory status. The highest class (5), “fully ambulatory”, is defined as the ability to independently ambulate and fully interact in the community. “Minimal ambulation” (4) is defined as ambulation limited to within the house/hospital, around the house/hospital, and to the mail box. “Ambulation with assistance” (3) is defined by ambulation requiring another person’s help for mobility. “Wheelchair bound” (2) is defined by dependency on a wheelchair for all mobility. “Bed bound” (1) is defined when the patient is not mobile at all, is fully restricted, and non-ambulatory. Ambulatory status at baseline is the level of function after onset of ALI or CLI and within one week prior to admission. Data will be abstracted by trained research staff and reviewed by vascular physicians.

All data will be collected via a standardized case report form and then entered into a password-protected database. Data will be collected consistent with the intersocietal “2012 ACCF/AHA/ACR/SCAI/SIR/STS/SVM/SVN Key Data Elements and Definition for Peripheral Atherosclerotic Vascular Disease” standards [14]. Outcome events will be reviewed and adjudicated by a clinical event committee consisting of individuals with expertise in vascular surgery and vascular medicine. The registry design has been approved by the local institutional review board at the University of Minnesota and Allina Health System. All included patients will provide written informed consent. Patients screened for entry who do not offer informed consent will be entered into a screening log.

### Key time segments

The symptom onset of an initial episode of ALI/CLI is defined by the patient’s self-report provided to the vascular specialist at hospital admission, is dictated into the encounter note, and this note (date and time) is later abstracted from the medical records. Vascular specialists (vascular surgeons, vascular medicine specialists, and interventional radiologists) are instructed to document the patient-reported index limb symptom onset within pre-specified time parameters: within one hour for patients presenting within 3 days, within one day for patients presenting within 3 to 30 days, and within one week for patients presenting greater than one month since symptom onset. For CLI patients who cannot state an exact time of leg symptom onset, it will be assumed that the onset time is 12 noon on the day specified. Inasmuch as ALI or CLI is known to recur (repeat episodes are common), the index leg symptom is arbitrarily defined as that which is temporally closest to the index hospitalization. This approach is similar to that used for ACS or stroke health services research.

While the pre-admission symptom duration serves as the primary pre-defined hypothesized predictor of advanced PAD health outcomes, a number of other clinical care time segments are considered of potential utility in evaluation of the efficiency of hospital-based PAD care, as it is known that CLI hospitalizations are lengthy (greater than seven days) and expensive [15]. The “admission to ABI/TBI” time segment is defined as the time from hospital arrival to initiation of the first hospital-based pedal or toe pressure measurement. The “admission to heparin” time is defined as the time from hospital arrival to the chart-documented initiation of a therapeutic intravenous heparin infusion for patients so treated. The “admission to vascular specialist at bedside” time segment is defined as the time from hospital arrival until the patient is evaluated by a vascular specialist, and this is set by the time of the dictated note. The “admission to revascularization” time segment is defined as the time from hospital arrival until the patient enters the operating room or catheterization laboratory, and includes only the use of an endovascular procedure, surgical procedure or primary amputation (medical treatment alone is not included in this definition). Hospital length of stay is defined as the number of days of hospitalization from admission to discharge.

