### Statistical analysis

Descriptive statistics will be presented as means and standard deviations for continuous variables, and frequencies and percentages for categorical data. Continuous data that are not normally distributed will be analyzed by nonparametric methods. Key time variables will be analyzed as continuous variables, and also categorized to allow assessment of dose–response patterns. Univariate models for all outcome variables with demographic, clinical and risk factor variables will be used to elucidate potential confounding variables. Multivariable logistic regression models will be used to assess the association between key time variables and short-term binary outcomes (amputation, MI, stroke and death), with adjustment for confounders. Survival analysis will be performed using Kaplan-Meier methods for preliminary analyses, and Cox proportional hazards models with adjustment for confounders. Multiple linear regression models will be used to assess the associations between time segment variables and length of stay, with adjustment for confounders. A two-sided p-value of <0.05 will be considered statistically significant. Data analysis will be performed using Stata (Stata Inc, College Station, TX, USA).

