During the last decade, cardiovascular care guidelines have become an important cornerstone of the management of heart disease and the positive impact of guidelines is known [28]. In contrast, the development and dissemination of PAD care guidelines, including recommendations regarding the ideal management of ALI and CLI, are rarely evaluated prospectively [1,2]. These guidelines have recognized that appropriate use of evidence-based risk-reduction medication represents a major opportunity for reducing future myocardial infarction, stroke, and death if used in individuals with recognized PAD. However, recent data have shown poor rates of use of evidence-based risk-reduction medication on admission or discharge in patients with CLI [10,29,30]. The registry will provide an opportunity to evaluate the contemporary use of risk-reduction medications to prevent these major ischemic events in the PAD population at highest short-term risk. We hypothesize that higher use of these medications would offer a potentially major contribution to improvement in rates of amputation-free survival; only a prospective registry with an adequate cohort sample is likely to provide such data, as a prospective RCT to evaluate this hypothesis is currently unlikely. Data further demonstrating such benefits of risk-reduction medication use might then be considered for future guideline inclusion, or within future PAD performance standards [31].

Currently there are no standardized quality-of-life instruments that are widely applied in populations of individuals with critical limb ischemia. This registry offers an opportunity to evaluate functional status on admission, at discharge and at follow-up, as well as other predictors of functional status at follow-up. While it is known that poor ambulatory status on presentation is associated with loss of primary patency and higher rates of amputation at six months follow-up, other factors beyond patency (e.g., avoidance of readmission, social support, etc.) may contribute to the achievement of improved functional outcomes [32].

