Several limitations are inherent to this (or any) registry. First, the enrollment of patients is intended to be consecutive, but this is never fully achieved for any registry. Nevertheless, the majority of the patients who present for hospital care may be enrolled if, as planned, both hospitalists and vascular specialists are engaged at registry launch. Second, as for any registry, selection for inclusion of a wide array of hospitals and health systems can facilitate accrual of a representative cohort. Third, any PAD registry is encumbered – in contrast to CAD or stroke registries – by the inconsistent use of objective diagnostic criteria in real world clinical practice (in contrast to RCTs). Whereas all individuals with an acute MI undergo an ECG, it is not now clear whether individuals with advanced PAD undergo consistent vascular laboratory testing. Thus, we have elected to initially permit the inclusion of all “clinically diagnosed” ALI and CLI without the requirement of pedal or toe pressure measurements. Analysis of cohorts who have, or have not, undergone such testing can demonstrate the utility of this diagnostic approach. We note that the past diagnostic inclusion criteria of an ankle pressure of ≤50 mmHg [33] would potentially exclude two-thirds of patients with CLI, as only 30% would fulfill the European Consensus Guideline pedal pressure criteria, as observed in the BASIL trial [34]. Thus, the registry will provide valuable information in a “real-world” setting by using broader inclusion criteria. Pre hoc defined subgroup analysis of the “clinical diagnosis” and “objective diagnosis” groups will provide insight regarding the value of current diagnostic pathways on choice of therapy and achievement of positive outcomes.

In conclusion, a multicenter advanced PAD registry may represent a significant opportunity to assess a series of hypothesis-based factors that may modify systemic or limb outcomes. In a manner analogous to methods used to better understand the natural history and impact of treatments for acute MI, stroke and heart failure, advanced PAD registry data that includes pre-hospital factors, revascularization strategies used during an index hospitalization, and that evaluates long-term use of risk modifying pharmacotherapies may provide new insights to help the design of future PAD clinical trials.

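### In-hospital waiting times that exist only for patients who reached treatment are modelled against early amputation and death, and the drug-use analysis has no stated time origin

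*Protocol article*

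**What the plan says.** **In-hospital segments.** The Key time segments section starts every in-hospital interval at hospital arrival. The heparin interval ends at "chart-documented initiation of a therapeutic intravenous heparin infusion for patients so treated". The revascularization interval stops when the patient is taken in for the procedure. By definition it "includes only the use of an endovascular procedure, surgical procedure or primary amputation (medical treatment alone is not included in this definition". The list of pre-specified segments has six entries. Only symptom onset to admission is complete at admission. Pressure measurement, heparin, specialist at the bedside, revascularization and length of stay all end later.

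**Their role.** The same section says that "pre-admission symptom duration serves as the primary pre-defined hypothesized predictor of advanced PAD health outcomes", and that "other clinical care time segments are considered of potential utility in evaluation of the efficiency of hospital-based PAD care".

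**Models.** The Statistical analysis section enters the key time variables in multivariable logistic models of short-term amputation, MI, stroke and death. It gives no start or length for the outcome window. For survival it names Kaplan-Meier methods and "Cox proportional hazards models with adjustment for confounders", without saying which exposures enter or from when.

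**Drugs.** Risk-reduction drug use is the third of the three main factors in the Background. Table 2 records it at admission, discharge, 1, 6 and 12 months. The Discussion states: "We hypothesize that higher use of these medications would offer a potentially major contribution to improvement in rates of amputation-free survival". Study outcomes gives amputation-free survival at one year with no start date. In-hospital amputations and deaths are recorded at discharge, whereas the follow-up calls are timed from discharge.

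**The concern.** An exposure that becomes known only after the clock has started carries event-free time with it. A patient whose wait was five days was, by construction, alive and treatable for five days. A patient who died on day two without treatment has no wait and cannot enter a regression on it. Comparing long with short waits then favours long waits even if timing has no effect. Adjustment for confounders does not remove this, because it comes from the definition of the exposure and not from patient characteristics.

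The same mechanism threatens drug use whenever use reported at a later contact is treated as if known at the start: only patients who reach the contact can report it.

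Both errors have a predictable direction. Delay looks harmless and drugs look beneficial. The article intends the results to point to targets for later trials, and the Discussion mentions possible use of the drug findings in guidelines or performance standards.

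**Working it through.** The article states no sample size, event count or effect size, so there is no figure of its own to reproduce. The check is how far a true null moves.

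**1. Wait to treatment**

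Inputs:
- Event risk by day 30 of *r* = 10, 20 or 30%. This is scaled on the 30-day major amputation range of 10-30% in the Discussion; its use as the risk of the event that prevents treatment is an assumption.
- Exponential waits with mean 0.5, 2 or 5 days (assumed).
- Hazard either constant or clustered early (Weibull shape 0.5, assumed).
- No effect of the wait.

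The mechanism can be seen by hand. For a patient treated at day *w*, the risk of an event by day 30 after admission is

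- constant hazard: 1 − (1 − *r*)^(1 − *w*/30)
- early-clustered: 1 − (1 − *r*)^(1 − √(*w*/30))

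With *r* = 0.30, a patient treated at once has risk 0.300 and odds 0.300/0.700 = 0.429. Then:
- *w* = 2, constant: risk 0.283, odds 0.395, OR 0.395/0.429 = 0.92
- *w* = 5, constant: risk 0.257, odds 0.346, OR 0.346/0.429 = 0.81
- *w* = 5, early-clustered: risk 0.190, odds 0.235, OR 0.235/0.429 = 0.55

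Simulation of 400,000 patients per setting, keeping only those treated before an event and splitting waits at the median, gave these odds ratios (long against short wait, outcome counted from admission; ranges are over *r*):

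| Mean wait | Constant hazard | Early-clustered |
|---|---|---|
| 0.5 day | 0.96-1.00 | 0.88-0.89 |
| 2 days | 0.89-0.91 | 0.75-0.77 |
| 5 days | 0.73-0.77 | 0.60-0.62 |

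Counting 30 days from treatment instead gives 0.99-1.02 under constant hazard but 0.73-0.91 with early clustering, because survivors of a long wait are already past the worst period. Moving the origin to treatment is therefore not a sufficient repair.

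**2. Drug use**

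Inputs, all assumed: one-year event risk 30, 40 or 50%; time from discharge; new starts at 1 and 6 months in patients still event-free; no drug effect; 60,000 patients per setting.

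| Use at discharge | Non-users starting at each contact | Ever-use as fixed covariate, HR |
|---|---|---|
| 30-50% | 30% | 0.66-0.72 |
| 0% | 50% | 0.46-0.47 |

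The same data with time-updated use give a rate ratio of 0.99-1.01. Use fixed at discharge and counted from discharge gives 0.98-1.02. Discharge use is thus a sound baseline when time starts at discharge.

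**The case against.** The strongest reply has four parts.

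*A reader might infer that immortal-time bias is built into two of the three main hypotheses.* The document does not support that. The main factors are pre-hospital symptom duration, use of revascularization strategies, and drugs. In-hospital waits are none of these; they serve to judge hospital efficiency. Symptom duration is complete at admission. Revascularization strategy is exposed only if treated and untreated patients are compared from admission, which is nowhere stated. This part of the reply stands.

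*A reader might also infer that drug use goes into a Cox model as a fixed covariate.* The article never says so. A Cox model can take time-updated covariates, and such detail may sit in an analysis plan that is not shown. Drug use is recorded at discharge and calls run from discharge, so a valid analysis is available. This also stands: the drug part is a risk from an unstated origin, not a demonstrated error.

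*Not every segment drops patients.* The restriction to treated patients is worded for heparin. The revascularization segment retains primary amputations, so limb loss as the first procedure does not remove a patient from it, although amputation is then both the end of the interval and a modelled outcome. The specialist segment is not limited to treated patients. This narrows the loss of patients in the revascularization segment mainly to deaths before a procedure.

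*The size depends on assumptions, and the registry is described as hypothesis-generating.* True. If most waits are hours and the hazard is constant, the distortion is negligible.

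None of this answers the logistic models. There the exposure definition, the restriction to treated patients, the model and the outcomes are all stated.

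**Conclusion.** The point holds in a limited form. For the in-hospital segments, the stated analysis conditions on surviving to treatment and biases toward delay appearing safe. Under a null the odds ratio is 0.89-1.00 for mean waits up to 2 days at constant hazard, and goes down to about 0.60 for multi-day waits with early-clustered events. These are secondary analyses, and the primary predictor is not touched.

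For drug use, a main factor, the article leaves the time origin open. If follow-up use were entered as a fixed ever-use covariate, a null would read as a hazard ratio of about 0.46-0.72. With discharge use counted from discharge there is no such bias.

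The sizes rest on assumed wait distributions, hazard shapes, drug-use shares and one-year risks, and on the 10-30% amputation range standing in for the risk of any event that prevents treatment. The direction does not depend on those choices; the amount does.

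**What to change.** Change the analysis wording:

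- **In-hospital treatment timing.** Start at admission with all patients and enter treatment as a time-dependent covariate. Alternatively, choose a fixed landmark in advance, keep patients still event-free at that time, and classify them by treatment received by then.
- **Drug use.** Start at discharge among patients discharged alive and free of amputation, and take discharge use as the exposure. Let later use enter only as a time-updated covariate from the contact at which it was reported.
- **Time origin.** State it for amputation-free survival and for the short-term logistic outcomes.

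The in-hospital intervals and the repeated drug-use records are already part of the planned data collection, so no new contact is needed. The cost is that events before the landmark or before discharge leave these analyses. They should be reported separately, so that early deaths and amputations stay visible.
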